## Abstract

**Background:**

Chronic post-surgical pain (CPSP) is recognised as one of the most common and debilitating complications of major surgery. Progression from acute to chronic pain after surgery involves sensitisation of central nervous system pathways with the N-methyl-D-aspartate (NMDA) receptor having a central role. Ketamine is a potent, non-selective NMDA antagonist commonly used for management of acute postoperative pain. Inconsistent but largely supportive evidence from small trials of a preventative effect of perioperative ketamine on CPSP risk suggests that a confirmative large trial is needed.

**Methods:**

The ROCKet (*R*eduction *O*f *C*hronic Post-surgical Pain with *Ket*amine) Trial is a multicentre, double-blind, placebo-controlled, individually randomised superiority trial conducted in 36 hospitals across Australia, New Zealand, and Hong Kong. The trial aims to recruit 4884 patients undergoing abdominal, thoracic, or major orthopaedic surgery. Eligible participants are randomised equally to perioperative intravenous ketamine or placebo for up to 72 h. Incidence of pain in the area of the index surgery is measured by structured telephone interview at 3 months (primary trial endpoint) and 12 months. Pain severity, nature, and associated psychological and quality of life indices are measured using the modified Brief Pain Inventory short form, Neuropathic Pain Questionnaire, Kessler K-10 Psychological Distress Scale, Pain Catastrophising Scale, EQ-5D-3L, and measures of healthcare utilisation and costs. The trial is being conducted by the Department of Critical Care, University of Melbourne, and the Australian and New Zealand College of Anaesthetists Clinical Trials Network. The trial is funded by the Australian National Health and Medical Research Council.

**Discussion:**

The ROCKet trial will clarify the effectiveness of ketamine in primary prevention of CPSP. In addition, it will provide high-quality, prospective data on the epidemiology of CPSP which will better inform further research into prevention and management of CPSP.

**Trial registration:**

Australian New Zealand Clinical Trials Registry (ACTRN12617001619336) on the date of 12/11/2017.

## Background

Chronic post-surgical pain (CPSP) is recognised as one of the most common and debilitating complications of major surgery [1]. A number of surgical and psychosocial factors are associated with an increased likelihood of developing CPSP including severity of early (acute) postoperative pain, increased duration of surgery, open (as opposed to laparoscopic) surgical approach, intraoperative nerve damage, preoperative anxiety and fear, introversion, previous persistent pain, and mental health conditions [2–4].

Investigators studying the epidemiology of CPSP have highlighted that ‘an alarming proportion of patients…develop chronic postsurgical pain…’ and ‘… even the lowest incidences are unacceptably high’ [2, 3]. A review of CPSP found ‘one-year incidence to be highly variable and surgery specific, ranging from a low of approximately 10–15% following modified radical mastectomy…to a high of 61–70% for thoracotomy…and amputation’ [3]. These data are disturbing but are confirmed by a Norwegian national epidemiological study, which found an incidence of 40% at least 3 months post-surgery, and by prospective follow-up data from the large international ENIGMA (Evaluation of Nitrous oxide In the Gas Mixture in Anaesthesia) and ENIGMA II trials, which found an overall incidence of CPSP of 11–12% at 1 to 4 years after a broad range of major surgery [5–7]. There is relatively little data on the natural history of CPSP, and it is likely that the variation in incidence reported by studies reflects heterogeneity in surgical type and the methodology and timing of data collection which typically ranges between 3 months and 1 year post-surgery. A taskforce of the International Association for the Study of Pain (IASP) has recommended that chronic pain be defined as pain persisting for at least 3 months, as part of a new World Health Organisation (WHO) ICD-11 definition of chronic pain as a discrete disease state [8]. This definition has been extended to include CPSP and post-traumatic pain [9].

Progression from acute to chronic pain after surgery and trauma involves sensitisation of central nervous system pathways, particularly at the level of the spinal cord, neuroinflammation, and spinal cord ‘wind-up’, with the N-methyl-D-aspartate (NMDA) receptor having a central role in this process [10–12]. Ketamine is a potent, non-selective NMDA antagonist which is commonly used as a second- or third-line agent for management of acute postoperative pain, because of its unique analgesic properties [13]. Ketamine administration can lead to psychomimetic or dissociative side effects in around 5% of surgical patients, including vivid dreams, hallucinations, and agitation, which limit dosage in a small proportion of patients in the postoperative setting [13].

The potential effect of ketamine on the development of CPSP is unclear. A Cochrane review examined the effect on CPSP incidence of several perioperative pharmacological interventions including gabapentinoids, membrane stabilisers, steroids, non-steroidal anti-inflammatories (NSAIDs), and NMDA receptor antagonists including nitrous oxide and ketamine. Across eight heterogeneous small studies totalling 914 patients, the authors found evidence of a potential benefit from intravenous (IV) ketamine, with an odds ratio (OR) versus placebo of 0.50 (95% confidence interval [CI] 0.33–0.76, *p* = 0.001) [14]. They cautioned that large trial data were lacking and needed. A more recent meta-analysis has reinforced this conclusion [15]. An extensive James Lind Alliance survey of 2000 health practitioners, patients, and public stakeholders in the UK nominated prevention of CPSP as a leading research priority for anaesthesia and perioperative medicine [16].

The ROCKet (*R*eduction *O*f *C*hronic post-surgical pain with *Ket*amine) trial is a large, multicentre, double-blind, parallel group, placebo-controlled, individually randomised superiority trial of the effect of perioperative IV ketamine on the incidence and severity of CPSP, measured at 3 months and 12 months following elective abdominal, thoracic, or major orthopaedic surgery. The trial is being conducted by the Australian and New Zealand College of Anaesthetists Clinical Trials Network (ANZCA CTN).

## Methods/design

### Objectives

The primary objective is to determine if IV ketamine, given immediately prior to and for up to 72 h following surgical incision, reduces the incidence of CPSP at 3 months after surgery, compared to placebo.

Secondary objectives include measuring the effect of perioperative ketamine on indices of acute postoperative pain severity, side effects, and quality of recovery. Ketamine effect on CPSP incidence at 12 months is also being measured. Measures of CPSP severity and neuropathic characteristics, and patient wellbeing and psychological distress relative to preoperative baselines, are assessed at 3 and 12 months post-surgery, including their relationship to trial treatment allocation. The trial protocol is described according to the SPIRIT (Standard Protocol Items Recommendations for Interventional Trials) reporting guidelines (see SPIRIT Checklist in the supplementary material) [17]. Table 1 outlines the protocol using the recommended WHO trial registration data set.

**Table 1 Tab1:** WHO trial registration data set

Data category	Information
Primary registry and trial identifying number	Australian and New Zealand Clinical Trials Registry: ACTRN12617001619336
Date of registration in primary registry	11 December 2017
Source(s) of monetary or material support	NHMRC Australia: Project Grant (GNT1120848, 2017) Clinical Trials and Cohort Studies Grant (GNT2023989, 2022); Research Grants Council Hong Kong: (Grant 14112718)
Primary sponsor	University of Melbourne, Victoria, Australia
Contact for public queries	[name] [contact]
Contact for scientific queries	[name] [contact]
Public title	ROCKet Trial
Scientific title	*R*eduction *O*f *C*hronic Post-surgical Pain with *Ket*amine (ROCKet) Trial
Countries of recruitment	Australia, New Zealand, Hong Kong
Health condition or problem studied	Chronic post-surgical pain (CPSP) at 3 months (ICD-11 definition) after index surgery
Intervention	
Active comparator:	IV ketamine commenced prior to surgical incision and continued for up to 72 h or until hospital discharge
Placebo comparator:	Matched IV saline placebo
Key inclusion criteria (see Table 2)	Consenting adult patients (≥ 18 years), ASA 1–3, undergoing elective or expedited surgery and anaesthesia with planned postoperative opioid analgesia and hospital stay of at least one postoperative night, for any one of the following: I. Abdominal surgery involving an expected skin incision at least 8cm in length, and including open inguinal herniorrhaphy II. Non-cardiac thoracic surgery, including mastectomy and breast reconstruction surgery and including all video-assisted thoracoscopic surgery (VATS) III. Hip, knee and shoulder joint arthroplasty and spinal surgery involving an expected skin incision at least 8 cm
Key exclusion criteria (see Table 2)	Age > 85 years, pregnancy, BMI > 45 kg/m^2^ or weight over 130 kg, ASA 4 or 5 Planned use of intra- or post-operative continuous IV lignocaine infusion Contraindications to IV ketamine administration
Study type	Interventional, phase III trial
	Primary purpose: prevention
	Allocation: randomised 1:1, stratified by (i) hospital, (ii) preoperative pain at surgical site Intervention model: parallel assignment Masking: double blind
Date of first enrolment	19 December 2017
Target sample size	4884
Recruitment status	Recruiting
Primary outcome	CPSP incidence at 3 months after index surgery
Key secondary outcomes	*Within 3 months after index surgery*: Acute postoperative pain severity (opioid consumption oral morphine equivalents, and mean, minimum and maximum NRS pain scores at rest and activity) on days 1–3 post-surgery (or until hospital discharge) Quality of recovery on day 1 using the QoR-15 Length of hospital stay defined as time from surgery start to hospital discharge Incidence of adverse/side effects related to the study drug during index hospital admission
	Severity of CPSP at 3 months after index surgery (mBPI) and neuropathic pain incidence (NPQ) Wellbeing and psychological distress at 3 months post-surgery (mBPI, EQ-5D-3L and K-10)
	*Within 12 months after index surgery*: CPSP at 12 months after index surgery; severity of CPSP at 12 months after index surgery (mBPI) and neuropathic pain incidence (NPQ) Wellbeing and psychological distress at 3 months post-surgery (mBPI, EQ-5D-3L and K-10)

*WHO* World Health Organization, *ICD-11* International Classification of Diseases 11th Revision, *NHMRC* National Health and Medical Research Council, *IV *Intravenous, *CPSP *Chronic post-surgical pain, *ASA *American Society of Anesthesiologists physical status classification, *BMI* Body mass index, *mBPI *Modified Brief Pain Inventory, *NRS* Numerical Rating Scale, *NPQ* Neuropathic Pain Questionnaire, *EQ-5D-3L* EQ-5D-3L questionnaire, *K-10* Kessler K-10 questionnaire

The trial protocol is designed to make a large multicentre trial of a perioperative intervention with a delayed primary outcome feasible, using a distance model of postoperative telephone follow-up for primary endpoint data collection that was successfully used in two previous large multicentre ANZCA CTN trials (ENIGMA and ENIGMA II) [6, 7]. The trial protocol was piloted in the ROCKet Pilot trial, conducted in three hospitals in Victoria, Australia, recruiting 80 patients undergoing abdominal, thoracic, or breast surgery. CPSP was measured at 6 months post-surgery in this pilot trial [18].

Identical data on CPSP at both 3 months and 12 months post-surgery has been collected from the trial outset. Originally, CPSP at 12 months post-surgery was chosen as the primary trial endpoint, to be consistent with data on CPSP incidence collected using similar methodology at 12 months after surgery from 3000 patients enrolled in the ENIGMA II trial [6, 19]. These data were used to estimate the expected CPSP incidence and data attrition rates for sample size calculation for the ROCKet trial. However, after ICD-11 was formally implemented by the WHO in 2022, the trial steering committee, who remained fully blinded to trial treatment allocation at all times, decided to change the timing of the ROCKet trial primary endpoint to 3 months post-surgery, with treatment effect at 12 months post-surgery becoming a secondary endpoint.

### Ethics, sponsorship, and trial registration

Approval was granted by the Austin Health Human Research Ethics Committee in 2017 (HREC17Austin161), and the trial was registered with the Australian New Zealand Clinical Trials Registry (ACTRN12617001619336, 11 December 2017). Trial sponsorship is provided by the University of Melbourne (Parkville 3050, Victoria, Australia).

### Governance

The design and conduct of the trial are the responsibility of the trial steering committee, consisting of the chief investigators, trial statistician, and trial manager. Monitoring of trial protocol delivery and data quality is managed by the trial operations committee. A data and safety monitoring committee (DSMC), consisting of 5 independent experts in clinical trials and an independent statistician, review unblinded data on safety endpoints and adverse events, monitor withdrawals, and review ethical conduct of the trial. In addition, they advised on the pre-planned interim analysis. A single pre-planned interim analysis by the DSMC was scheduled that allowed stopping early for superiority, at the availability of 12-month follow-up CPSP data from the first 1500 recruited patients (expected at roughly around the mid-point of overall trial recruitment).

### Population

The inclusion criteria represent consenting adult patients (18 years or more) presenting for elective or expedited surgery under anaesthesia for a variety of major surgeries (Table 2) associated with CPSP. The exclusion criteria cover a range of relative or absolute contraindications to ketamine administration or to participation in the trial (Table 2).

**Table 2 Tab2:** ROCKet trial recruitment inclusion and exclusion criteria

**Inclusion criteria**
Written informed consent
Age ≥ 18 years
ASA physical status 1–3
Elective or expedited surgery and anaesthesia for any one of the following:
I. Abdominal surgery involving an expected skin incision at least 8cm in length, and including open inguinal herniorrhaphy
II. Non-cardiac thoracic surgery, including mastectomy and breast reconstruction surgery and including all video-assisted thoracoscopic surgery
III. Hip, knee, and shoulder joint arthroplasty and spinal surgery involving an expected skin incision at least 8 cm
Plan for postoperative opioid analgesia
Plan for hospital stay of at least one postoperative night
Expected to be alive at 12 months after index surgery
**Exclusion criteria**
Age > 85 years
Unable to provide written informed consent
Pregnancy or lactation
BMI > 45 kg/m^2^ and weight over 130 kg
ASA physical status 4–5
Planned use of intra or postoperative continuous IV lignocaine infusion
Uncontrolled hypertension (SBP > 180 mmHg) on admission
Poorly controlled atrial fibrillation (ventricular response rate > 120/min) on admission
Uncontrolled heart failure
Intracranial surgery or raised intracranial pressure
History of haemorrhagic stroke
Severe impairment of liver function
Previous adverse reaction to ketamine
Documented complex regional pain syndrome
History of epilepsy or convulsions
History of psychosis or of illicit drug use or known illegal activities
Previously randomised to the ROCKet trial

*ASA *American Society of Anesthesiologists, *BMI *Body mass index, *SBP *Systolic blood pressure

The trial is being conducted in metropolitan and regional acute care hospitals in Australia, New Zealand, and Hong Kong. Participating sites have access to an acute pain service within their hospital and the equipment available to administer trial drug intraoperatively and postoperatively. Patients may be co-enrolled in other studies where there is no conflict in trial design, intervention, or outcome determination with the ROCKet trial. The trial is managed by the trial coordinating centre at the Department of Critical Care, the University of Melbourne, Victoria, Australia.

### Recruitment

Patients are screened for eligibility preoperatively via surgical booking lists and approached by research staff by telephone or at preadmission surgical or anaesthesia outpatient clinics or on the surgical ward for preoperative inpatients. The patient information and consent form is provided along with a face-to-face discussion with eligible patients and carers or family, to answer any questions about the intervention and potential risks and benefits and to allow written, informed consent to be given by the patient. A model consent form is provided as a supplementary material.

### Randomisation and treatment allocation

Following informed consent and liaison with clinical staff identified as responsible for perioperative care of the patient, randomisation is achieved by research staff preoperatively on the day of surgery using a password-protected web-based system. Randomisation is stratified by (a) hospital and (b) presence or absence of preoperative pain in the area of the surgery (Numerical Rating Scale [NRS] score for average pain in last 24 h of ≥ 3/10). Patients are randomly assigned with a 1:1 allocation to either the intervention arm (ketamine intra- and postoperatively) or the control arm (placebo intra- and postoperatively). The randomisation code was computer-generated using randomly permuted blocks by an independent statistician from the University of Melbourne.

### Blinding

Trial participants, research, hospital pharmacy, medical and nursing staff, data collectors, trial statistician, and Steering, Operations and Endpoint Adjudication Committee (EAC) members are all blinded to trial group assignment until after completion of primary endpoint data collection and database finalisation and locking.

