### Statistical analysis

A detailed statistical analysis plan will be developed prior to unblinding of the data collected up to 3 months after surgery. In what follows, the analysis plan using data up to and including the primary endpoint data is described. A separate plan will be written before unblinding for the data collected up to 12 months post-surgery.

The analysis will include all randomised patients, excluding patients who had their surgery cancelled post-randomisation and did not return later for their planned surgery. For the analysis of the efficacy outcomes, patients will be reported and analysed according to their randomised study arm (i.e. ‘as randomised’). For the analysis of safety outcomes, patient data will be reported and analysed according to the intervention received (i.e. ‘as treated’), whereby those who did not receive at least one study treatment will be excluded from the analysis.

The primary estimand for the ROCKet trial is defined according to the addendum to the ICH E9 on estimands and sensitivity analysis in clinical trials [32]. The trial aims to answer the specific research question: does IV ketamine, given immediately prior to and for up to 72 h following surgical incision, compared to placebo, reduce CPSP at 3 months after surgery, measured by the relative difference in the incidence/risk (i.e. RR) of CPSP at 3 months after surgery between treatment arms, regardless of the post-randomisation (intercurrent) events listed below, while assigning the patients who died to have CPSP at 3 months?

Primary estimand attributes are:Treatment: IV ketamine, given immediately prior to and for up to 72 h following surgical incision, compared to placebo, allocation by randomisationPopulation: consenting adult patients presenting for elective or expedited surgery under anaesthesia for a variety of major surgeries associated with CPSPVariable: CPSP at 3 months post-surgeryIntercurrent events: not receiving trial solution during surgery will be handled using a treatment policy strategy, while death (expected incidence to be around 0.5% at 3 months) will be handled using a composite strategy by assigning the patients who died to have CPSP at 3 monthsPopulation level summary: relative difference in the incidence/risk (i.e. RR) of CPSP at 3 months after surgery between treatment arms (IV ketamine versus placebo)

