## Trial status

Trial recruitment commenced on 19 December 2017. In total, 36 hospitals have recruited patients to the trial across Australia, New Zealand, and Hong Kong. The current protocol version is v5.0, 7 July 2023. The trial is expected to complete recruitment in the first half of 2025.

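### The stated end of blinding is tied to the 3-month primary endpoint, so it does not protect 12-month CPSP interviews that fall after that lock

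*Protocol article*

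**What the plan says.** The Blinding section of the protocol article covers "Trial participants, research, hospital pharmacy, medical and nursing staff, data collectors, trial statistician, and Steering, Operations and Endpoint Adjudication Committee (EAC) members". It gives all of them one end to the blind: they "are all blinded to trial group assignment until after completion of primary endpoint data collection and database finalisation and locking".

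The Objectives section records that "Originally, CPSP at 12 months post-surgery was chosen as the primary trial endpoint" and that, after ICD-11 came into force in 2022, the blinded steering committee "decided to change the timing of the ROCKet trial primary endpoint to 3 months post-surgery". The 12-month effect became secondary. Table 1 lists 12-month CPSP incidence and severity among the key secondary outcomes.

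The section on post-operative follow-up has research staff telephoning patients at both time points for a structured interview. The section on the primary endpoint describes adjudication by two treatment-blinded EAC members, with a third as tiebreak, and leaves 12-month results to a later report.

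The Statistical analysis section says that a detailed plan will be ready before the data up to 3 months are unblinded. It adds: "A separate plan will be written before unblinding for the data collected up to 12 months post-surgery". Trial status gives the timetable: recruitment began on 19 December 2017, and "The trial is expected to complete recruitment in the first half of 2025".

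**The concern.** The end of the blind is defined by the primary endpoint. With that endpoint at 3 months, the last 12-month interview comes 9 months after the last interview needed for the trigger. No other section extends the blind for any role. Each patient has a single allocation, so a code released for the 3-month analysis also reveals the arm for the 12-month data unless access is restricted, and no restriction is stated.

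The outcome at stake is open to influence. The patient reports pain to an interviewer, and the CPSP definition then requires a judgement on whether that pain differs in site, nature or intensity from any preoperative pain. Knowledge of allocation could affect the report and, if 12-month cases are adjudicated in the same way, the classification. The 12-month outcome was also the original primary endpoint and the basis of the 4884 target.

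A second matter is the 12-month analysis plan. The same patients give identical CPSP data at both times, so analysis choices made after the 3-month effect is known would no longer be fully independent of the data.

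**Working it through.** **Reading the sections together**

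| Question | Where | Answer |
|---|---|---|
| Until when are all roles blind? | Blinding | Completion of primary endpoint data, plus database lock |
| When is the primary endpoint? | Objectives; Table 1 | 3 months |
| Is there a distinct 3-month unblinding? | Statistical analysis | Yes; its own plan precedes it |
| How is 12-month CPSP obtained? | Post-operative follow-up | Telephone interview by research staff |
| Does any role stay blind to the end of 12-month follow-up? | No section | Not stated |

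The guaranteed blind therefore ends at the 3-month lock, while a key secondary outcome may still be in collection.

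**How many patients could be affected**

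The protocol gives no figure for this, so there is none to reproduce. The total used is its own: 4396 / 0.90 = 4884.4, stated as 4884.

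Inputs from the article:
- target of 4884 (Sample size and study power)
- recruitment from 19 December 2017 to the first half of 2025 (Trial status)
- interviews at 3 and 12 months; randomisation on the day of surgery

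Assumptions, not in the article:
- uniform accrual
- recruitment ending between 31 January and 30 June 2025
- a lag of L months from the last 3-month interview to lock and release

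Let recruitment end at T. Lock falls at T + 3 + L. A patient randomised at t has the 12-month interview at t + 12, which is later than lock if t > T − (9 − L). Hence

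outstanding = monthly rate × max(0, 9 − L).

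Rates:
- end on 31 January 2025: 4884 / 85.4 months = 57.2 per month
- end on 30 June 2025: 4884 / 90.3 months = 54.1 per month

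| Lag L (months) | Window 9 − L (months) | End June 2025 | End January 2025 |
|---|---|---|---|
| 0 | 9 | 487 (10.0%) | 515 (10.5%) |
| 3 | 6 | 324 (6.6%) | 343 (7.0%) |
| 6 | 3 | 162 (3.3%) | 172 (3.5%) |
| 9 | 0 | 0 | 0 |

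These are randomised patients still awaiting the 12-month contact. They are not patients who have been told their arm. Some would also be lost to follow-up: the protocol assumes 10% at 12 months, so 515 would yield about 515 × 0.90 = 464 interviews.

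**The case against.** The strongest reply is that the Blinding section sets a minimum and announces no release. Nothing says that participants, interviewers or adjudicators will be given allocations once the 3-month data are locked. A reader might infer that the rule actively unblinds them; the text does not support that. What stands is that the rule stops guaranteeing their blinding at that point.

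The lock condition could also mean the whole database, 12-month data included, since the Database section describes a single central system. That reading is possible. It fits poorly with the Statistical analysis section, which makes unblinding of the data up to 3 months a separate event, and with the deferral of 12-month results to a later report.

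On the analysis plan, a reader might infer that the 12-month plan will be written with the 3-month result in hand. The sentence can equally mean that the plan for the 12-month data is written before any unblinding, which would be sound. It is ambiguous and does not by itself show a fault.

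Two further inferences go too far. Earlier protocol versions are not shown, so it cannot be asserted that the same wording once covered all follow-up. EAC adjudication is described explicitly only for the 3-month endpoint, so its use at 12 months is plausible but inferred.

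Finally, who receives codes at a staged lock may be set out in the full protocol. That would excuse silence. Here, however, the article states a rule, for every role, with a trigger that falls before 12-month collection need be complete.

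**Conclusion.** The point holds as a gap in protection. It does not show that unblinding will occur. The stated blind ends at a trigger that can precede the last 12-month interviews by up to 9 months, and no section extends it.

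Exposure is between 0 and about 515 patients (0 to 10.5% of 4884), all recruited near the end. The range rests on two assumptions: uniform accrual and the lag to lock. Accrual was not in fact uniform. The article reports severe reductions over two years from March 2020 and no return to the pre-pandemic peak, so the rate in the final months may differ from the average. Data queries and dual adjudication will take time, which pushes the figure down, but the article fixes no lag that would guarantee zero. No bias in the 12-month risk ratio can be estimated from the documents.

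The 3-month primary outcome is unaffected, as are sample size, power and alpha. The point deserves correction because 12-month CPSP is a key secondary outcome that depends on self-report, and a blind once broken cannot be restored.

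**What to change.** Reword the Blinding section so that participants, site staff, telephone interviewers and any EAC members adjudicating 12-month outcomes stay blind to individual allocation until the 12-month data are collected, adjudicated and locked. State that at the 3-month lock allocations are released only to the analysis team, and name the roles in that team.

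Reword the sentence on the 12-month plan in the Statistical analysis section to say that this plan is finalised before the 3-month data are unblinded.

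The cost is wording, access control on the randomisation codes, and earlier drafting of the 12-month plan. Individual allocations are withheld from participants and sites for up to about 9 months longer.
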